### 1.1 Blinding

This clinical trial is conducted with single blinded (covering the eyes of the evaluators) to minimize bias. For blinding of the evaluators, all evaluators are blinded to the group allocation and blinded the clinical information.

Only the random assignment officer and the therapist (the researcher) who conducted the intervention are aware of the information about the group allocation. But the independent evaluators are kept blinded. After all test results are saved as images or entered into the database and database locking, the person in charge can know the randomly assigned results.

### 1.2 Assessment

The assessment will be performed by three independent physiatrists who have certificate.

### 1.3 Randomization and Enrollment

In order to prevent an imbalance in the number of study subjects between the experimental group and the control group, a block randomization method is adopted. Randomization was performed using Microsoft Excel program. 24 GMFCS IV and 18 GMFCS V subjects were randomly assigned to two groups with a block size of 4 and an allocation ratio of 1:1. In the header of cells A1, B1, C1, and D1 of the Excel spreadsheet, enter Sequence, Random number, Block, and Group, respectively. ① Enter the numbers from 1 to 24 and 1 to 18 in cell A, which is the Sequence column, in order, and ② enter the function = Rand() in B of the Random number column to assign a random function. ③ In block column C, repeat the numbers 1 to 6 and 1 to 4 in order. At this time, the numbers 1 to 4 or 6 are repeated 4 times, which means that 24 and 18 study subjects were assigned a block size of 4. ④ In the Group column, input the experimental group and the control group, respectively, followed by 12 and 9 people. Then, drag from B1

to D1 to select it, and select Home -> Sort & Filter -> Filter. When there is a scroll bar in each cell, click the scroll bar in C1 to select ascending sort, and then click the scroll bar in C1 to sort in ascending order to complete the randomization table (Kang, 2017). A random number table is created, and a new random function is generated at the start of the study. At this time, the random number on the sheet may change and the assignment may be changed, so copy or capture the value and keep it.

Enrollment : competitive enrollment

## 1.4 Outcomes

### 1.4.1 Primary Outcome

Hip dislocation by radiographic evaluation (%).

### 1.4.2 Secondary Outcomes

- Functional changes such as the degree of scoliosis, pain index, satisfaction with wearable medical devices for hip joint protection, hip and knee joint range of motion, discomfort in caring for patients, and changes in the overall quality of life of patients through simple radiographic examination.

#### A. Joint range of motion

Measure the joint range of motion of the patient's hip and knee using a goniometer.

VI. abduction with hip at 90° flexion

VII. Hip abduction with hip at 0° flexion

VIII. Hip adduction with hip at 0° flexion

IX. Hip flexion contracture (Thomas test)

X. Popliteal angle

#### B. Femur anteversion

[figure not shown]

Fig. 1. Anterior-posterior (AP) and lateral (LAT) imaging protocols. In the LAT view, the pelvis is rotated slightly posteriorly to prevent overlap with the femur head.

[figure not shown]

Fig 2. System overview: the anterior-posterior (AP) and lateral (LAT) views are initially pose-estimated using user inputted six points and its 3D correspondences. The image contour is segmented based on the projected contour of the 3D femur. The AP and LAT views are calibrated more accurately using contour correspondences. The shape is optimized so that its projected contour to match the segmented contour. These steps are iteratively performed until convergence.

In the case of femur anteversion, CT is generally taken, but the radiation dose is high, so we decided to use a method to measure femur anteversion using simple radiographic examinations such as femur AP and femur lateral x-ray. (K. Youn et al) Measured at initial, 6 months, and 12 months.

### **C. Questionnaire evaluation**

I. Pain index (Visual analog scale): In the case of children with cerebral palsy GMFCS IV and V, communication is difficult, so the patient's hip pain felt by the guardian is evaluated.

### **D. Likert scale**

Satisfaction evaluation of wearable medical device for hip joint protection

Example of this study questionnaire: Very satisfied - Satisfied - Moderate - Somewhat dissatisfied - Very dissatisfied

### **E. Child Health Index of Life with Disabilities (CPCHILD)**

This tool consists of 9 items as a tool to evaluate the quality of life of patients with severe cerebral palsy. The guardian evaluates, and each item is scored on a scale of 0 to 5, and each item is as follows. Investigate hip contracture-related items among CPCHILDS, such as daily activities, posture/movement, comfort and emotion, the child's overall quality of life, and the importance of items related to the child's quality of life

## **1.5 Study Design**

### **1.5.1 Overall Design**

Multicenter, prospective, parallel, double blinded, randomized clinical trial.

### **1.5.2 Study Scheme**

- Patients diagnosed with severe cerebral palsy were included in the study.
- Assignment to experimental group and control group when consent to the study
- Radiologic and clinical evaluation were performed to evaluate hip dislocation.
- The experimental group manufactured and applied hip joint wearable medical devices and continued the existing rehabilitation treatment.
- The control group continued the existing rehabilitation treatment.
- After 6 months and 1-year, clinical evaluation and radiological evaluation were performed to determine effectiveness.
- 

## **1.6 Study Population**

### **1.6.1 Inclusion Criteria**

Subjects must satisfy all of the following criteria to be included in the study

- I. age 1 to 15 years
- II. Gross Motor Function Classification System (GMFCS) IV and V
- III. quadriplegia or diplegia for more than 6 months
- IV. patients who have provided written consent with permission of the child and caregiver

### 1.6.2 Exclusion Criteria

- I. In the event that the study was discontinued at the request of the subject or his/her representative
- II. In case of concurrent use of surgery, drug, or medical device that may affect clinical trial results
- III. If clinical trials are not properly conducted
- IV. In case the initial and late evaluation cannot be performed due to the absence of the subject
- V. Withdrawal of consent at the request of the subject or his/her representative
- VI. In case tracking is not possible due to non-scheduled visit
- VII. In case the subject dies due to reasons not related to the clinical trial
- VIII. When the investigator determines that the suspension of the test is beneficial to the subject
- IX. If the other investigator determines that there is a problem with the clinical trial

## 1.7 Data Analysis and Statistical Analysis Methods

- The clinical evaluation is statistically compared between the initial and simple X-ray results after 1 year (compare with paired t-test or Wilcoxon signed rank test according to normality test).
- In addition, the difference in the change values for the initial, 6 months, and 1 year after simple X-ray imaging and clinical evaluation is statistically compared.
- Repeatedly measured values are verified with a linear mixed model or Generalized estimating equation (GEE) between the experimental group and the control group.
- If the P-values are  $< 0.05$ , it is judged to be a significant level.
- All data, including those included in statistical processing (ITT) through safety and efficacy evaluation, will be analyzed for those who are dropped out unless there is a valid reason or justification.
- In the case of missing values in the FAS group, it is difficult to satisfy the assumption of Missing Completely at Random (MCAR), so it is excluded and analyzed.

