| 
and
 
Expected results
 | 
complication that occurs in more than 80% of patients, but there is no treatment available to prevent it. In case of complications, there is no other treatment other than surgical treatment.
 
It is expected that this medical device will prevent hip dislocation, Reduce complications in patients with severe cerebral palsy, improve quality of life, It is expected to reduce medical expenses.
 |
|------------------------------------|---------------------------------------------------------------------------------------------------------------------------------------------------------------------------------------------------------------------------------------------------------------------------------------------------------------------------------------------------------------------------------------------------------------------|

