## **14) Observation items, clinical examination items, and observational examination methods**

1. Primary efficacy endpoint: hip dislocation through radiographic evaluation (%)
2. Secondary efficacy endpoints: degree of scoliosis through plain radiograph; Degree of femur anteversion, pain index, Functional changes such as satisfaction with wearable medical devices for hip joint protection, hip and knee joint range of motion, discomfort when caring for a patient, and changes in the patient's overall quality of life were investigated.

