## 5.0 General statistical considering

4.8 This clinical trial uses a two-sided hypothesis for the test of difference in effectiveness. It is defined as a two-sided hypothesis, as stated in the section "Sample size calculation". ( $H_0: \mu_t = \mu_c$ ,  $H_1: \mu_t \neq \mu_c$ ).

4.9 The statistical method is to test normality using the Kolmogorov-Smirnov test, then test parametric or Wilcoxon rank-sum test (nonparametric test) depending on the normal distribution.

4.10 The number of observations, mean, standard deviation, median, minimum,

and maximum values are presented for continuous variables, and frequency and percentage are presented for categorical data.

4.11 If a missing value occurs during validity analysis or a missing value occurs due to the elimination of the subject before the clinical trial is completed, this study measures the validity evaluation only once in the early and late period, and analyzes only the observed data (observed processes) without any correction to the missing values.

4.12 However, other safety assessment and other data are analyzed using data that do not replace missing values.

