4.13 Assessment of effectiveness

Repeatedly measured values are verified with a linear mixed model or Generalized estimating equation (GEE) between the experimental group and the control group. If the P-values are  $< 0.05$ , it is judged to be a significant level.

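### One p < 0.05 rule covers the primary migration index and every secondary efficacy endpoint, with no order, gate, adjustment or exploratory label, so false secondary findings are likelier than the stated level implies

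*Combined protocol and SAP*

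**What the plan says.** SAP v13.0 section 1.7 covers radiographic and clinical measures together: "the difference in the change values for the initial, 6 months, and 1 year after simple X-ray imaging and clinical evaluation is statistically compared". Section 4.13, on effectiveness, adds "Repeatedly measured values are verified with a linear mixed model or Generalized estimating equation (GEE) between the experimental group and the control group". Both sections then give one criterion: when p is below 0.05, "it is judged to be a significant level". Section 4.8 fixes the sidedness: "This clinical trial uses a two-sided hypothesis for the test of difference in effectiveness". Protocol section 17(1) and the statistical row of the Study Overview repeat the same rule.

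The endpoints concerned are labelled as efficacy endpoints. Protocol section 12, item 14), begins the list "Secondary efficacy endpoints: degree of scoliosis through plain radiograph; Degree of femur anteversion, pain index" and continues with device satisfaction, hip and knee range of motion, discomfort in caring for the child, and quality of life. SAP 1.4.2 A splits range of motion into five measures, for example "Hip abduction with hip at 0° flexion". SAP 1.4.2 E names no CPCHILD score; it says "Investigate hip contracture-related items among CPCHILDS, such as daily activities, posture/movement, comfort and emotion" and goes on to overall quality of life and item importance. The Study Overview expects the device to "Reduce complications in patients with severe cerebral palsy, improve quality of life".

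I found no statement in the current SAP or protocol that orders the secondary tests, makes them depend on the MI result, divides alpha among them, or calls them exploratory or supportive.

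**The concern.** As written, a nominal p-value below 0.05 on scoliosis, pain, any range-of-motion measure or quality of life is a significant result on an efficacy endpoint, whatever happens on MI. With several such endpoints, the chance that at least one crosses the line by luck is well above the level of a single test. Because the CPCHILD items are listed by example, the number of tests is not fixed in advance either.

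At stake is what the trial may conclude if MI is negative or equivocal. A report that followed the plan to the letter could present an isolated secondary result as a finding on the same footing as the primary.

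**Working it through.** **The plan's own figures.** The plan states no family-wise error rate for the secondary endpoints. Its only related calculation is the MI sample size (SAP 2.3.2, protocol section 10), which reproduces. The difference is 7.83 − 1.566 = 6.264 with SD 8.73, two-sided 5%, power 80%. The two-sample t calculation gives 31.5, rounded up to 32 per group. That calculation concerns MI alone.

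**Inputs from the documents.**
- Level per test: 0.05, two-sided (SAP 1.7, 4.8, 4.13), so 0.025 in the direction favouring the brace.
- Secondary endpoints: Cobb angle, femur anteversion, pain, range of motion, caring discomfort, and quality of life by CPCHILD (SAP 1.4.2; protocol section 12, item 14).
- Device satisfaction is left out, because controls do not wear the device during the trial.

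**Assumptions, because the documents are silent.**
- One between-arm test per endpoint.
- Number of tests m: 6 if range of motion and CPCHILD count once each; 10 if the five range-of-motion measures are tested separately (6 − 1 + 5); 14 if the five CPCHILD areas are as well (10 − 1 + 5).
- A common correlation ρ between test statistics: 0.5 as the working value, 0 to 0.8 as the range.

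**Formulas, with no true effect on any endpoint.**

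If the tests are independent:
- either direction: 1 − 0.95^m
- favouring the brace: 1 − 0.975^m

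For m = 6 these are 1 − 0.735 = 0.265 and 1 − 0.859 = 0.141.

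With common correlation ρ, c = 1.96 and a standard normal common factor X:
- either direction: 1 − E[{Φ((c − √ρ·X)/√(1−ρ)) − Φ((−c − √ρ·X)/√(1−ρ))}^m]
- favouring the brace: the same without the second Φ term.

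**Results** (chance of at least one significant secondary result):

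| m | Direction | ρ = 0 | ρ = 0.5 | ρ = 0.8 |
|---|---|---|---|---|
| 6 | either | 0.265 | 0.207 | 0.139 |
| 6 | favouring brace | 0.141 | 0.104 | 0.069 |
| 10 | either | 0.401 | 0.287 | 0.173 |
| 10 | favouring brace | 0.224 | 0.144 | 0.086 |
| 14 | either | 0.512 | 0.348 | 0.197 |
| 14 | favouring brace | 0.298 | 0.174 | 0.099 |

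A simulation with two-sample t-tests, 32 per arm and correlation 0.5 (3,000 runs) gave 0.22, 0.28 and 0.33 in either direction for m = 6, 10 and 14, close to the integration.

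**Relative to one test.** At ρ = 0.5 the either-direction rate is 0.207/0.05 = 4.1 to 0.348/0.05 = 7.0 times the single-test level. The rate favouring the brace is 0.104/0.025 = 4.2 to 0.174/0.025 = 7.0 times. In the mildest case (m = 6, ρ = 0.8) both ratios are 2.8: 0.139/0.05 and 0.069/0.025.

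The within-arm paired tests in SAP 1.7 and any separate analysis of left and right hips are not counted.

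**The case against.** The best defence is that the plan's efficacy decision is already tied to MI. SAP 2.3.1 states the null and alternative hypotheses only for change in MI, 4.8 refers back to them, 2.3.2 F claims superiority on MI alone, and the only secondary objective (2.1.2) is safety. One primary endpoint is named and the rest are called secondary, which by convention means supportive. The Study Overview's expectation about complications and quality of life is a hope, not a rule for making claims. Much of this stands: MI's type I error is untouched, and nothing expressly licenses an efficacy claim when MI fails. But the convention is never written down, while the significance rule is, and it is written for all measures.

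The counts can also be challenged, fairly. SAP 1.4.2 lists quality of life as one outcome and does not say that CPCHILD areas are tested one by one. Caring discomfort has no instrument of its own and may come from CPCHILD, so m = 14 may double count. That is why the result is a range starting at 6.

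Three stronger readings are tempting and are not supported:
- A reader might take 21-35% as the chance of a false *benefit*. It counts differences in both directions; the figure for benefit is half that.
- A reader might double the tests because there are visits at 6 months and 1 year. With 28 tests at correlation 0.5 the rates would be 0.49 in either direction and 0.25 favouring the brace. But SAP 1.7 and 4.13 assign repeated values to a mixed model or GEE, so one test per endpoint is the likelier reading.
- A reader might add that caregivers, who rate pain and CPCHILD, know the arm. That is plausible, since controls receive the device only at the end (protocol section 21, compensation plan). But protocol section 12, item 12), says that research subjects stay blinded, so it is an inference. It is also a question of bias, not of multiplicity.

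**Conclusion.** The point holds as a gap in the decision rule. The same p < 0.05 criterion applies to MI and to every secondary efficacy endpoint, without hierarchy, gatekeeping, adjustment or exploratory label. For a brace with no effect, the chance of at least one significant secondary difference in either direction is about 21-35% (14-51% over correlations 0.8 to 0), and of at least one favouring the brace about 10-17% (7-30%). The comparable single-test figures are 5% and 2.5%.

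The exact percentages depend on the assumed 6 to 14 tests, one per endpoint, and the assumed correlation. That there is inflation does not: even the mildest case shown is 2.8 times the single-test level. The point does not bear on the validity of the primary MI test. It should be corrected, because it changes what the trial may conclude from its secondary results.

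**What to change.** - In SAP 1.7 and 4.13, protocol section 17(1) and the Study Overview, limit the p < 0.05 decision rule to the single primary MI comparison.
- State that secondary endpoints are exploratory and are reported as between-arm differences with 95% confidence intervals, with any p-values marked nominal and unadjusted.
- In SAP 1.4.2 E and the matching protocol text, replace the open-ended list of CPCHILD items with one named score at 12 months.
- If a secondary claim is wanted, name one measure per domain at 12 months, test these only if the MI comparison is significant, and apply Holm adjustment at 0.05 across them.

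The cost is SAP and protocol wording; no extra patients or data are needed. The downside is that a nominally significant secondary result can no longer be presented as proof of benefit.

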## 2.0 Data Safety Monitoring Plan

### 2.1 Data Safety Monitoring Plan

3.1.1 Responsibility of Data and Safety Monitoring: [name], The Principal Investigator

#### 3.1.5 Practice of Data and Safety Monitoring: [name], The Sub- Investigator

Risk occurrence of this study is low since only one evaluation of X-ray and brace(elastic bandage) is performed. This study is corresponded to a low risk study. Measure pain and discomfort before and after the test. To decide continue, change or discontinue of the

study, use Numerical Rating Scale (NRS) as a key validation variable.

If the pain and the discomfort last 3 days after the test, perform additional test and confirm safety. The test fee should be paid by the insurance that have signed up for. To manage this, [name] professor is appointed as the monitoring manager and the principal investigator and the sub-investigator perform monitoring every six months. In the adverse event during the study, if the case is a serious adverse effect, report it to the IRB immediately and if the case is a minor adverse effect, the principal investigator and the sub-investigator perform monitoring first and report it to the IRB.

#### 3.1.6 Notifying IRB, principal investigator and Regulatory Authorities

- I. Adverse drug effect/adverse medical device effect report (fatal/life-threatening): Within 7 days (Initial report), within 8 days (tracking report)
- II. Adverse drug effect/adverse medical device effect report (not fatal/life-threatening): Within 15 days
- III. Safety information report: At least once every 6 months
- IV. Report of unexpected adverse reactions: Within 15 days

#### 3.1.7 Criteria for discontinuance of the study

- I. Discontinue the study when the target study data is obtained.
- II. If the number of study subjects could not be recruited within the IRB approval period, determine the discontinuation or alternation of the study.
- III. If the study is discontinued, the subjects follow the treatment procedures of the correspond hospital.

## 5.0 General statistical considering

4.8 This clinical trial uses a two-sided hypothesis for the test of difference in effectiveness. It is defined as a two-sided hypothesis, as stated in the section "Sample size calculation". ( $H_0: \mu_t = \mu_c$ ,  $H_1: \mu_t \neq \mu_c$ ).

4.9 The statistical method is to test normality using the Kolmogorov-Smirnov test, then test parametric or Wilcoxon rank-sum test (nonparametric test) depending on the normal distribution.

4.10 The number of observations, mean, standard deviation, median, minimum,

and maximum values are presented for continuous variables, and frequency and percentage are presented for categorical data.

4.11 If a missing value occurs during validity analysis or a missing value occurs due to the elimination of the subject before the clinical trial is completed, this study measures the validity evaluation only once in the early and late period, and analyzes only the observed data (observed processes) without any correction to the missing values.

4.12 However, other safety assessment and other data are analyzed using data that do not replace missing values.

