### 11) Control group setting and randomization method

Experimental group and the control group, a block randomization method is adopted.

Randomization was performed using Microsoft Excel program. A total of 68 study subjects (34 in the experimental group, 34 in the control group) were randomly assigned to a block with a block size of 4 and an allocation ratio of 1:1. In addition, in order to stratify GMFCS IV and V, 68 GMFCS IV and V are assigned respectively.

In the header of cells C4, D4, E4, and F4 of the Excel spreadsheet, enter Sequence, Random number, Block, and Group, respectively. ① Enter the numbers from 1 to 68 in cell C, which is the Sequence column, in order, and ② set the seed (GMFCS IV: 11074, GMFCS V: 11075) using the random number generation function of the data analysis tool for reproducibility in D of the Random number column. to assign a random function. ③ In Block column E, repeat the numbers from 1 to 17 in order. ④ In the Group column, input the experimental group and the control group by 34 consecutively. Then, drag from C4 to F4 to select it, and select Home -> Sort & Filter -> Filter. When a scroll bar appears in each cell, select ascending sort by clicking the scroll bar of E4, and then click the scroll bar of E4 to sort in ascending order to complete the randomization table (Kang, 2017).

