### 2.3 Sample Size Determination

#### 2.3.1 Statistical Hypotheses

the null hypothesis is as following.

$H_0$  = There is no meaningful relationship in migration index (MI) between the two groups. ( $H_0: U_t = U_c$ ).

$H_1$  = There is significant differences in MI between the two groups. ( $H_1: U_t \neq U_c$ ).

$U_t$  = MI (Post, test group) - MI (Pre, test group),  $U_c$  = MI (Post, control group) - MI (Pre, control group).

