#### 2.3.2 Sample Size Determination

A. The calculation of the sample size is based on the previous epidemiologic study ([name] IS, Park D, Ko JY, [name] JS. Are Seating Systems With a Medial Knee Support Really Helpful for Hip Displacement in Children With Spastic Cerebral Palsy GMFCS IV and V? *Arch Phys Med Rehabil* 2019; **100**(2): 247-53.).

B. In this study, the annual progression of MI in patients with severe cerebral palsy (GMFCS IV and V) was measured to be  $7.83 \pm 8.73$  %. Assuming the MI decreased by 80 % applying Hip protection brace, the MI of the study group was set to  $1.566 \pm$

8.73 %.

C. We used PASS 15.0 for two-sample T-Test assuming equal variance.

D. With an  $\alpha$  of less than 0.05 in the two-tailed tests and a power of 80%, the target sample size of each group is 32 patients.

E. Considering a dropout rate of 5 %, the final sample size was determined to be 68 patients per group.

F. This clinical trial compares the post-treatment changes between the study and the control groups. This study was the superiority trial to show the significant improvement of the MI in the study group than the control group.

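### SAP v13.0 does not identify one primary between-group test of migration index: the model, contrast and visit are left open, and neither baseline MI nor the GMFCS stratum enters any analysis

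*Combined protocol and SAP*

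**What the plan says.** All of the following is current text.

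- **Endpoint.** SAP v13.0, 1.4.1 gives "Hip dislocation by radiographic evaluation" in per cent, with no visit attached. Section 2.3.1 states the hypothesis as a comparison of post-minus-pre MI between arms, with no time given for post. Item 4.8 refers back to that hypothesis.
- **Sizing.** SAP 2.3.2 uses an unadjusted two-sample t-test on annual progression.
- **Between-group rule 1.** Item 4.9 (under 5.0): "test normality using the Kolmogorov-Smirnov test, then test parametric or Wilcoxon rank-sum test (nonparametric test) depending on the normal distribution".
- **Between-group rule 2.** Item 4.13, which covers how efficacy is judged, reads: "Repeatedly measured values are verified with a linear mixed model or Generalized estimating equation (GEE) between the experimental group and the control group". It specifies no model terms, contrast, covariance structure or selection rule.
- **Other comparisons.** Section 1.7 begins with baseline against 1 year: "compare with paired t-test or Wilcoxon signed rank test according to normality test". It then compares change values across the initial, 6-month and 1-year assessments by an unnamed method, and repeats the mixed model or GEE. The protocol says the same in its overview and in section 17.
- **Measurement times.** Item 4.11 says efficacy is assessed once early and once late. Protocol section 12, item 14 schedules MI at baseline, 6 and 12 months.
- **Stratification.** Protocol section 12, item 11: "in order to stratify GMFCS IV and V, 68 GMFCS IV and V are assigned respectively". No analysis section names GMFCS level or baseline MI as a covariate.

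**The concern.** A confirmatory trial needs one test, fixed before the data are seen. Here two items give different between-group methods, each containing an unresolved choice, and two follow-up visits are in play with a single 0.05 threshold. An analyst acting in good faith could pick the model, contrast or visit after seeing results, and two such analysts could reach different conclusions from the same data. This matters more because the therapists, and the researcher in charge at each institution, know the allocation, so prespecification is one of the main safeguards.

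Leaving out the stratification factor and the baseline value of the outcome does not invalidate the test, but it gives up precision that costs nothing in a small trial.

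**Working it through.** **1. The plan's own sample size.** Inputs from SAP 2.3.2: α "less than 0.05 in the two-tailed tests and a power of 80"%; control progression 7.83, SD 8.73; "Assuming the MI decreased by 80 % applying Hip protection brace", giving 1.566.

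- Difference = 7.83 − 1.566 = 6.264. Standardised difference = 6.264 / 8.73 = 0.7175.
- Noncentrality at n = 32 per arm = 0.7175 × √(32/2) = 2.870, with 62 df. Power is 80.7% (79.4% at 31). So 32 per arm reproduces.
- 64 / 0.95 = 67.4, rounded up to 68 in total, as in the protocol.

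The sizing therefore corresponds to a single unadjusted comparison of 12-month change.

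**2. What the text permits.**

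| SAP v13.0 | Method | What is left open |
|---|---|---|
| 4.9 | Parametric or rank-sum test after a normality test | Which parametric test, which visit |
| 4.13 and 1.7 | Mixed model or GEE | Which of the two, terms, contrast, visit |
| 1.7 | Comparison of change values at 6 months and 1 year | Method, primary visit |
| 4.11 | Assumes one early and one late value | Does not fit a repeated-measures model |

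**3. If either visit may count.** Type I error = 1 − P(|Z₆| < 1.96 and |Z₁₂| < 1.96), with Z₆ and Z₁₂ bivariate normal and correlation ρ. The documents do not give ρ. The result is 9.3% at ρ = 0.4, 8.3% at 0.7 and 7.8% at 0.8.

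**4. The normality switch alone.** Simulation of 5,000 null trials at 32 per arm, using plug-in mean and SD with no Lilliefors correction: type I error 5.1% with normal data and 5.6% with skewed data (lognormal, σ = 0.8). How often the switch operates depends on details the SAP does not give. For exponential data at n = 32, the uncorrected test rejects normality about 13% of the time and the Lilliefors version about 81%. Uncorrected on 64 pooled values, it is about 58%.

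**5. Free choice among methods.** Same simulation, 6/12-month correlation 0.7, six readings (t, rank-sum, mixed-model average effect, mixed-model 2-df test, GEE 12-month contrast, GEE 2-df test). The chance that at least one gives p < 0.05 under the null was 10.2% (normal) and 11.4% (skewed). Part of this is the uncorrected GEE variance, which alone gave 5.9% (12-month) and 6.8% (2-df) with normal data. At the planned effect, taking the 6-month effect as half the 12-month one, power ranged from 71% (mixed model, 2-df) to 83% (GEE, 12 months).

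**6. Gain from adjustment.** Adjusted SD = 8.73 × √(1 − R²), where R² is the share of the variance in change explained by the covariates.

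| R² | Adjusted SD | Power at 32 per arm |
|---|---|---|
| 0 | 8.73 | 80.7% |
| 0.05 | 8.51 | 82.6% |
| 0.10 | 8.28 | 84.6% |
| 0.20 | 7.81 | 88.5% |

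As a rough anchor, take the baseline SD of 17.10 from protocol v1.2 and assume equal SDs at both times. The change-baseline correlation is then −8.73 / (2 × 17.10) = −0.255, so R² = 0.065 from baseline alone and power is about 83%.

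**7. Within-arm tests.** Suppose the brace does nothing and both arms progress equally. Let p be the power of a one-sample t-test at n = 32, SD 8.73. The chance that control is significant and brace is not is p(1 − p): 24.9% at 3 points per year (p = 0.470), 10.5% at 5 (p = 0.881) and 0.2% at the planned 7.83 (p = 0.998).

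**The case against.** Item 4.13 is the only clause headed as the assessment of effectiveness. The SAP's amendment list shows the mixed model or GEE replacing the t-test/rank-sum wording of the former item 4.6 after statistical advice, so 4.9 is most likely text that was never cleaned up. Twelve months is strongly implied by the annual progression in the sizing, the baseline-to-1-year comparison and the end visit at 360 days. The 6-month and 1-year changes could be meant as one joint repeated-measures analysis. Omitting covariates is inefficient but not an error, since the planned 32 per arm is adequate unadjusted.

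Most of this stands as a statement of probable intent. It does not close the gap, because nothing in the current text withdraws 4.9, and 4.13 taken alone is still two methods with no contrast.

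Four stronger readings are tempting but not supported:

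- **That 4.13 means a group main effect on raw MI with baseline included, leaving power near 10%.** SAP 2.3.1 and item 4.8 define the hypothesis on post-minus-pre change, which that contrast does not test.
- **That the normality switch materially inflates error.** Step 4 shows that it does not.
- **That within-arm p-values will be read as efficacy.** No section says so, and the risk is negligible at the plan's own progression rate.
- **That the background figures of 3.9% (GMFCS IV) and 9.5% (GMFCS V) show how much MI variance GMFCS explains.** The protocol presents them as yearly increases in dislocation risk, not as mean MI changes.

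**Conclusion.** The point holds as under-specification of the primary analysis. Model, contrast and visit are not fixed, and items 4.9 and 4.11 conflict with a repeated-measures analysis. If significance at either visit were allowed to count, type I error would be about 8 to 9% for correlations of 0.4 to 0.8. If any of the six readings in step 5 could be chosen, it would be about 10 to 11% under that simulation's assumptions. These figures measure what the wording permits; they do not show that the sponsor intends to choose after the fact.

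Adjustment for baseline MI and GMFCS is a recommended gain in efficiency, worth about 2 to 8 percentage points of power for an assumed R² of 5 to 20%. All figures assume complete data and one MI value per child per visit.

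**What to change.** - **Primary analysis.** Name one confirmatory test in item 4.13: a linear mixed model for MI at 6 and 12 months with baseline MI, GMFCS stratum, arm, visit and arm-by-visit as fixed effects, and a stated covariance structure (unstructured suits two visits). The primary result is the arm difference at 12 months, two-sided 0.05, which matches the annual-progression sizing.
- **Hypothesis.** Define post in 2.3.1 as 12 months.
- **Clean-up.** Delete the normality switch in 4.9 and the GEE alternative for the primary test. Correct the single-measurement wording in 4.11. Align section 1.7 and the protocol's overview and section 17.
- **Sensitivity analyses.** Keep a rank-sum test on 12-month change and a GEE, both named as such.
- **Other results.** Report the 6-month difference as secondary or descriptive, and within-arm changes as descriptive.

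The cost is wording only. The data are already collected and the sample size does not rise. What is lost is the freedom to switch methods later.
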